### Intervention

The intervention consists of academic detailing, medicines review with web-based pharmaceutical treatment algorithms and tailored patient information leaflets. The academic detailing will involve a research pharmacist visiting intervention GPs in their own practices. The visit will include a short educational presentation about PIP as a concept, the criteria used to measure it and a summary of studies conducted in Irish primary care on the topic, as knowledge of PIP may be a barrier to appropriate prescribing in older patients [34]. Subsequent to this, practices will be asked to complete ten medicines reviews within a 6 to 8 week period, with a reminder issued if they are not completed within that period. An extended period may be negotiated, should a practice require it. During the medicines review, the GPs will use web-based treatment algorithms specifically designed for this study and accessible using a link and designated password. The algorithm will guide the process from the GP perspective, and does not incorporate patient involvement. It has a page-by-page structure, which will be completed when the GP fills in a review outcome form, detailing decisions made by the GP and patient together, including the reasons for maintaining a PIP, which is a key element of this study. Once the review outcome form has been filled in, the medicines review is complete. The medicines review will take place in the GP practice and will be scheduled at a date and time that is convenient to both the GP and the patient. In group practices where more than one GP is participating, the reviews may be divided between them in a manner that is most suitable to the practice workload. The pilot study indicated that the preparation for the review might be more time consuming for the GP than usual but there was no indication that the consultation itself would be significantly longer. These components are presented in Table 1.

**Table 1 T1:** Intervention components

**Intervention component**	**Description**
Academic detailing	A research pharmacist will visit the intervention practices. During the academic detailing, the pharmacist will:
	• Discuss the concept of PIP with the GPs, focusing on the prevalence and consequences of PIP in primary care
	• Discuss the pharmaceutical treatment algorithm
	• Discuss the medicines review process
	• Demonstrate the web-based platform for accessing the pharmaceutical treatment algorithm for use in a medicines review with each participant patient
Medicines review with web-based pharmaceutical treatment algorithms	GPs will be asked to:
	• Schedule a medicines review for the patient’s next appointment
	• Log on to the designated website using individualized user-names and passwords
	• Access the individualized web-based pharmaceutical treatment algorithms for each patient during the review
	• Conduct a medicines review following the page-by-page web-based pharmaceutical treatment algorithms. Each pharmaceutical treatment algorithm has the following structure:
	Section A: The individual PIP with reason for concern
	Section B: Alternative pharmacological and nonpharmacological treatment options
	Section C: Background information (where relevant)
	• Complete the process by submitting the review outcome form for each PIP per patient
	Each GP will also be provided with a full, paper-based compendium of pharmaceutical treatment algorithms for reference
Patient information leaflets	For every alternative therapy option, a brief patient information leaflet has been written. These leaflets describe the PIP and the reasons why it may be inappropriate. They also outline the alternative therapies the GP may offer instead

Note: The decision on whether to follow the recommended treatment alternatives will be at the discretion of the GP, weighing up the risks and benefits and patient preference.

### Control group: usual care with simple feedback

The control-group GPs will continue to provide usual care but will also be provided with simple feedback. Data for patients in the control group will be reviewed during recruitment and a personalized patient list for the ten recruited patients will be given to the GP. The list will summarize the medication class to which the individual patient’s potentially inappropriate medication belongs, not the specific PIP and will not provide actionable recommendations for change. Participants will not receive an academic detailing visit, will not be prompted to carry out a medicines review with the individual patients, and will not have access to the pharmaceutical treatment algorithms with alternative therapy options. GPs will continue to provide usual care. In terms of repeat prescribing for public general medical services (GMS) patients, this means that a GP can give a prescription on a monthly basis or for a maximum of three months. At present, the Health Service Executive Primary Care Reimbursement Services (HSE-PCRS) has an on-line GP Application Suite where GPs can review administrative information on their GMS patient panel. They can also access prescribing analysis reports, which contain detailed financial and cost information related to their prescribing. Specific prescribing alerts and recommendations for older patients are not provided.

### Contemporaneous national control HSE-PCRS dataset

The control arm will receive simple feedback about their patients based on baseline data collection. Feedback has been found to promote slight improvements in professional practice but is most effective when it is provided intensively [35,36]. By participating in this research, the control group might also alter their behaviour, resulting in changes in prescribing patterns (that is, the possible Hawthorne effect). To address this, we will also analyze national prescription patterns for all GMS doctors via the HSE-PCRS prescription database after the trial. This is a national prescribing database based on GP and pharmacy claims in a number of community schemes, including the GMS scheme. Data from the PCRS GMS database can be used to compare practices participating in the study with nonparticipating practices, acting as a contemporary national control. Some 330,000 people aged 70 and over were eligible for the GMS scheme in 2009 [37]. Comparisons with previous PIP patterns nationally [11] will determine whether there have been changes over time at the population level.

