## Background

### Prescribing in older people

Older people are among the biggest consumers of healthcare services, particularly drug therapy [1]. They tend to have multiple conditions, requiring multiple drug treatments [2]. They also experience age-related changes in physiology and body composition that influence the body’s ability to process medications efficiently, in terms of both pharmacokinetics (the body’s ability to absorb, distribute, metabolize and excrete a drug) and pharmacodynamics (the drug’s physiological effects) [3,4]. Thus, prescribing for older people is a complex and challenging task, with the potential for adverse outcomes including drug-drug interactions, adverse drug reactions and potentially inappropriate prescribing (PIP) [5].

The term ‘potentially inappropriate prescribing’ covers a number of suboptimal prescribing practices, particularly the use of medicines that introduce a greater risk of adverse drug-related events where a safer and equally effective alternative is available to treat the same condition [6]. Inappropriate prescribing in older people can result in increased morbidity, adverse drug events, hospitalizations and mortality [7-9]. Potentially inappropriate prescribing may be measured with explicit (criterion-based) or implicit (judgment-based) tools [9]. A recently developed explicit process measure, the Screening Tool of Older People’s Prescriptions (STOPP), has been published for use in European settings [10].

When these criteria were applied to an Irish pharmacy claims database (containing the prescription records of 97% of those aged ≥70 nationally), it was found that 36% of those aged ≥70 years received at least one potentially inappropriate medication. Total PIP expenditure was estimated at over €45 million (or 9% of expenditure on pharmaceuticals in that age group) [11]. The clinical and economic burden of PIP is an important public health concern and it is important to minimize PIP where possible, to increase patient safety and encourage cost-effective prescribing.

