### Study population

Practices are eligible to participate if they have approximately 80 or more older patients (aged ≥70 years) on their patient panel (based on the need to recruit 10 patients per practice, and allowing for refusals) and they are based in the greater Dublin area (to facilitate the academic detailing process).

Practices are excluded where they have been involved in the development and piloting of the intervention or other concurrent medication quality related studies.

Patients will be considered eligible if they are aged 70 years or over and they are being prescribed one or more selected potentially inappropriate prescriptions on a repeat basis (only patients with an existing PIP will be included, as the intervention is specifically targeting the management of PIP).

Patients will be excluded if they have significant mental or physical illness that is likely to impair their ability to participate in the study, or they are unable to attend the GP surgery for consultation (for example, they are nursing home residents) or they are participating in another medication quality related study.

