### Sample size

As all the patients in this study will be selected on the basis of already having one or more potentially inappropriate prescriptions, the sample size calculations are based on a 100% prevalence rate. Separate sample size calculations were performed for the two primary outcomes:

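### The national HSE-PCRS comparison is not restricted to patients with PIP at baseline, so as described it cannot isolate a feedback or Hawthorne change in a control arm where every patient starts with PIP

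*Protocol article*

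**What the plan says.** The section of the protocol article on the contemporaneous national control begins with a problem. Control GPs receive feedback, and taking part may itself change how they prescribe. The national data are the stated answer: "we will also analyze national prescription patterns for all GMS doctors via the HSE-PCRS prescription database after the trial". Two uses follow. The first, meant as a concurrent comparator, is between practices: "Data from the PCRS GMS database can be used to compare practices participating in the study with nonparticipating practices". The second is historical: "Comparisons with previous PIP patterns nationally [11] will determine whether there have been changes over time at the population level". None of these is limited to patients who had PIP at the start.

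The trial population is limited in that way. Under Study population, "only patients with an existing PIP will be included, as the intervention is specifically targeting the management of PIP", and under Sample size "the sample size calculations are based on a 100% prevalence rate". Nationally, the Background reports that "36% of those aged ≥70 years received at least one potentially inappropriate medication".

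The Sample size section assumes no improvement in the control arm and says that this will be monitored in the process evaluation.

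**The concern.** The two populations behave differently over time even if no GP changes anything. The trial follows a closed group that all have PIP at entry, so the proportion with PIP can only stay at 100% or fall. (The other primary outcome, the mean number of PIPs per patient, can move either way.) The national population is open: patients who stop a PIP are replaced by patients who start one, and prevalence can stay level while individuals come and go. A fall in the control arm beside a flat national figure would therefore be expected from turnover alone.

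Comparing whole practices removes that asymmetry but creates another weakness. At most ten patients per practice are in the trial, and the control feedback lists only those patients. A change limited to them is a small part of the practice's prescribing. The phrase about participating practices also covers both arms, so it does not isolate the control practices whose behaviour is in question.

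At stake is how a small or null trial result is interpreted. If the arms end close together, readers will ask whether the feedback moved the control arm. The national data are the only quantitative check described for that. The other check is by interview, and the Qualitative evaluation section concedes that the control-GP interviews may be prone to recall bias.

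**Working it through.** The article gives no figure for the national comparison, so there is none to reproduce. What follows illustrates the two possible readings.

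**Inputs from the article**
- Trial prevalence at entry: 100% (Sample size).
- National prevalence at age 70 or over: P = 0.36 (Background). This may rest on a different criterion list from Table 2.
- Target difference: 10 points, from 100% to 90% (Sample size).
- Trial patients per practice: at most 10 (Recruitment and allocation).
- Older patients per practice: about 80 or more (Study population).

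**Assumed:** the share L of patients with PIP who no longer have it at follow-up without any intervention. The article gives no value, so a range is shown.

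**Reading 1: control arm against unselected national data.** If national prevalence is steady, the share g of PIP-free patients who acquire PIP must balance the losses: P × L = (1 − P) × g, so g = 0.36 × L / 0.64. The selected cohort goes from 100% to 1 − L.

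| Assumed L | Balancing g | National change | Trial cohort at follow-up | False gap |
|---|---|---|---|---|
| 5% | 2.8% | 0 | 95% | 5 points |
| 10% | 5.6% | 0 | 90% | 10 points |
| 20% | 11.3% | 0 | 80% | 20 points |

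The gap equals L whatever the value of P. Patients with PIP in nonparticipating practices, followed over the same period under the same criteria, would also fall to 1 − L, so the false gap would be 0.

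**Reading 2: participating against nonparticipating practices.** Both sides are unselected, so turnover cancels. The question becomes how much of a control-arm change would show.
- Change limited to the ten listed patients: a 10-point fall is 10 × 0.10 = 1 patient. In a panel of 80 that is 1/80 = 1.25 points; in an assumed panel of 300 it is 1/300 = 0.33 points. Because about 80 is the minimum panel, 1.25 is roughly the most that could be seen.
- Change spread over all patients with PIP in the practice, taking 36% as the practice's prevalence and new prescribing as unchanged: 0.36 × 0.10 = 3.6 points at any panel size.

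**National trend.** A comparison with earlier national figures describes secular change in the population. It contains no contrast with the control arm.

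**The case against.** The strongest reply is that the article never proposes to set the trial cohort's fall against national change. It names a comparison between practices and a population trend. On that wording the turnover bias does not arise, and population prevalence is a suitable measure of secular trend. This stands. A reader might infer that natural turnover will be reported as a Hawthorne effect, or that a 10-point artefact is built into the plan. The article supports neither: it states no rule for attributing a difference, and the 10% stopping rate that would match the target difference is only an assumption.

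A second reply is that a journal article may leave the comparator's definition to a fuller document, and that the permissive wording is compatible with a cohort matched on baseline PIP. This stands in part. Missing detail would be no finding, but the article does name both the comparators and their purpose, and the comparators as named do not serve that purpose.

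Third, a Hawthorne change need not stop at ten patients. That is fair: the 1.25-point figure applies only to a change limited to the listed patients, and the 3.6-point figure shows the less diluted case.

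Fourth, it is tempting to argue that the trial's PIP definition cannot be reproduced nationally. Of the 34 criteria in Table 2, 18 carry a figure from the national claims study cited there, 11 carry figures only from the other two sources, and 5 have none. But a missing published figure does not show that a criterion cannot be computed from claims. Several of the 16, such as an NSAID with an SSRI, are defined by drugs alone. The count does not establish a mismatch.

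Finally, the national analysis is supplementary. The listed primary and secondary outcomes are collected from practice records, questionnaires and review forms, and control GPs are also interviewed. That limits the consequence but does not repair the comparison.

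**Conclusion.** The point holds in limited form. The national data are brought in to address a feedback or Hawthorne change in the control arm, and neither described use would isolate one. Against unselected data, the false gap equals the unknown stopping rate: 5 to 20 points for assumed rates of 5% to 20%, given steady national prevalence. Between whole practices that bias is absent, but a 10-point change in the ten listed patients shrinks to about 1.25 points or less, and control practices are not singled out.

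The randomized comparison is not affected, because both arms are selected in the same way and turnover acts on both. The weakness lies in the supporting evidence on control-arm change, not in the trial's main result.

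**What to change.** Define the national comparator as a cohort selected as the trial's patients are:

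- From nonparticipating practices in HSE-PCRS, take patients aged 70 or over with at least one PIP in the baseline window, and follow them over the same period as the trial.
- Restrict this comparison to the Table 2 criteria that can be computed from claims, list them, and recompute the trial arms on that same subset.
- Compare the proportion still with PIP and the mean number of PIPs per patient with the trial control arm specifically.
- Keep the comparison with earlier national patterns as a description of secular change only.

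The cost is extra programming on a database already due to be analysed, and a smaller criterion set for this one comparison. A difference between practice records and claims data remains and should be stated as a limitation. The change is timely: the analysis is planned for after the trial, and patient recruitment was only starting when the article was submitted.

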### Outcome measures

The study focuses on a select number of PIP criteria identified in the literature that have been determined to be of clinical relevance by academic GPs and pharmacists, and are prevalent in Irish primary care (see Table 2).

**Table 2 T2:** Selected prescribing criteria and indicators

**Criterion**	**Concern**	**Prevalence in Ireland***
PPI for peptic ulcer disease at full therapeutic dosage for >8 weeks	Earlier discontinuation or dose reduction for maintenance or prophylactic treatment of peptic ulcer disease, oesophagitis or GORD is indicated	16.69% [11]
		7.68% [49]
		4.06% [10]
NSAID (>3 months) for relief of mild joint pain in osteoarthritis	Simple analgesics are preferable and usually as effective for pain relief	8.76% [11]
		1.05% [49]
		1.26% [10]
Long-term (>1 month), long-acting benzodiazepines, for example, chlordiazepoxide, flurazepam, nitrazepam and clorazepate, and benzodiazepines with long-acting metabolites, for example, diazepam	Risk of prolonged sedation, confusion, impaired balance, falls	5.22% [11]
		5.19% [49]
		3.00% [49]
		6.01% [10]
		9.09% [10]
Any regular duplicate drug class prescription, for example, two concurrent opiates, NSAIDs, SSRIs, loop diuretics, ACE inhibitors. Excludes duplicate prescribing of drugs that may be required on a p.r.n. basis, for example, inhaled β2 agonists (long and short acting) for asthma or COPD, and opiates for management of breakthrough pain	Optimization of monotherapy within a single drug class should be observed prior to considering a new class of drug	4.78% [11]
		2.18% [49]
		6.01% [10]
TCAs with an opiate or calcium channel blocker	Risk of severe constipation	2.05% [11]
		0.37% [49]
Aspirin at dosage >150 mg/day	Increased bleeding risk, no evidence for increased efficacy	1.69% [11]
		0.3% [49]
		0.14% [10]
Theophylline as monotherapy for COPD or asthma	Risk of adverse effects due to narrow therapeutic index	1.18% [11]
		0.56% [10]
Use of aspirin and warfarin in combination without histamine H_2_ receptor antagonist (except cimetidine because of interaction with warfarin) or PPI	High risk of GI bleeding	1.09% [11]
		0.3% [49]
Doses of short-acting benzodiazepines, doses greater than: lorazepam (Ativan®), 3 mg; oxazepam (Serax®), 60 mg; alprazolam (Xanax®), 2 mg; temazepam (Restoril®), 15 mg; and triazolam (Halcion®), 0.25 mg	Total daily doses should rarely exceed the suggested maximums	0.98% [49]
		1.54% [10]
Prolonged use (>1 week) of first-generation antihistamines, that is, diphenhydramine, chlorpheniramine, cyclizine, promethazine	Risk of sedation and anticholinergic side-effects	0.96% [11]
		0.15% [49]
Warfarin and NSAID together	Risk of GI bleeding	0.75% [11]
		1.68% [10]
Calcium channel blockers with chronic constipation	May exacerbate constipation	0.68% [49]
		0.28% [10]
NSAID with history of peptic ulcer disease or GI bleeding, unless with concurrent histamine H_2_ receptor antagonist, PPI or misoprostol	Risk of peptic ulcer relapse	0.67% [49]
		0.42% [10]
Bladder antimuscarinic drugs with dementia	Risk of increased confusion, agitation	0.46% [11]
		0.84% [10]
TCAs with constipation	May worsen constipation	0.45% [49]
		0.14% [10]
Digoxin at a long-term dosage >125 μg/day (with impaired renal function)	Increased risk of toxicity	0.36% [11]
		0.15% [49]
		0.55% [10]
Thiazide diuretic with a history of gout	May exacerbate gout	0.36% [11]
		0.45% [49]
		0.14% [10]
Glibenclamide (with type 2 diabetes mellitus)	Risk of prolonged hypoglycaemia	0.29% [11]
		0.22% [49]
Aspirin with a past history of peptic ulcer disease, without histamine H2 receptor antagonist or PPI	Risk of bleeding	0.22% [49]
		0.28% [10]
Prochlorperazine (Stemetil®) or metoclopramide with parkinsonism	Risk of exacerbating parkinsonism	0.21% [11]
TCAs with dementia	Risk of worsening cognitive impairment	0.18% [11]
		0.28% [10]
TCAs with glaucoma	Likely to exacerbate glaucoma	0.14% [11]
		0.07% [49]
TCAs with cardiac conductive abnormalities	Pro-arrhythmic effects	0.14% [10]
Long-term corticosteroids (>3 months) as monotherapy for rheumatoid arthritis or osteoarthritis	Risk of major systemic corticosteroid side-effects	0.14% [10]
Bladder antimuscarinic drugs with chronic prostatism	Risk of urinary retention	0.14% [10]
NSAID with heart failure	Risk of exacerbation of heart failure	0.07% [49]
		0.14% [10]
TCAs with prostatism or prior history of urinary retention	Risk of urinary retention	0.07% [49]
		0.14% [10]
Systemic corticosteroids instead of inhaled corticosteroids for maintenance therapy in COPD or asthma	Unnecessary exposure to long-term side-effects of systemic steroids	0.07% [49]
		0.56% [10]
Bladder antimuscarinic drugs with chronic glaucoma	Risk of acute exacerbation of glaucoma	<0.01% [11]
NSAID with SSRI	Increased risk of GI bleeding	N/A
Bladder antimuscarinic drugs with chronic constipation	Risk of exacerbation of constipation	N/A
Prednisolone (or equivalent) > 3 months or longer without bisphosphonate	Increased risk of fracture	N/A
NSAID with ACE-inhibitor	Risk of kidney failure, particularly with the presence of general arteriosclerosis, dehydration or concurrent use of diuretics	N/A
NSAID with diuretic	May reduce the effect of diuretics and worsen existing heart failure	N/A

ACEI, angiotensin-converting-enzyme inhibitor; COPD, chronic obstructive pulmonary disease; GI, gastro-intestinal; GORD, gastro-oesophageal reflux disease; N/A, not available; NSAID, nonsteroidal anti-inflammatory drug; PPI, proton pump inhibitor; p.r.n., *pro re nata*, as needed; SSRI, selective serotonin reuptake inhibitor; TCA, tricyclic anti-depressant. *Prevalence: the proportion of the study population with one or more potentially inappropriate medications.

The primary outcomes to be determined are the proportion of participant patients with PIP (as a composite measure, that is, any number of PIP criteria as listed in Table 2, to address the issue of multiple PIP in individual patients) and the mean number of potentially inappropriate prescriptions per patient.

Secondary outcomes (summarized in Table 3) will include individual measures of the composite measure, that is, drug-specific outcomes, process evaluations, process-of-care measures and patient-reported outcomes (Health status (EQ-5D) [38], Patients’ Beliefs about Medicine Questionnaire (BMQ) [39], Well-being Questionnaire (WBQ-12) [40]).

**Table 3 T3:** Secondary outcome measures

**Secondary outcome**	**Measure**
Drug-specific outcomes	The absolute number of PIPs per patient of the top five occurring PIP drugs: [11]
	Proton pump inhibitor (PPI) for peptic ulcer disease at full therapeutic dosage for >8 weeks
	Long-term (>3 months) use of NSAIDs for relief of mild joint pain in osteoarthritis
	Long-term (>1 month) use of long-acting benzodiazepines, for example, chlordiazepoxide, flurazepam, nitrazepam, chlorazepate and benzodiazepines with long-acting metabolites for example, diazepam
	Any regular duplicate drug class prescription
	TCAs with an opiate or calcium channel blocker
	Mean number of PIPs per patient of the top five PIP drugs (as above)
Patient-reported outcomes	Health status (EQ-5D)
	Patients’ Beliefs about Medicine Questionnaire (BMQ)
	Well-being Questionnaire (WBQ-12)
Process-of-care measures	Number of GP visits (6 months prior to enrolment and at 4 and 12 month follow-up)
	Number of hospital admissions (6 months prior to enrolment and at 4 and 12 month follow-up
Process evaluations	Decisions made per PIP
	Number of times alternatives were prescribed
	Reported primary reason for decision made for example, risks outweigh benefits, patient preference, hospital/consultant initiated

